Participants who do take paracetamol need to discontinue its use at least 24 hours prior to the baseline assessment and follow-up assessments at 1, 3 and 6 months after the treatment;

(x) be willing to not receive any physical therapy on the involved MPJ or trial of shoe modifications or foot orthoses during the study period.

Exclusion criteria for participants in this study will be:

(i) Severe radiographic evidence of OA (score 3 for either osteophytes or joint space narrowing) at the first MPJ using a previously published radiographic classification [19];

(ii) previous surgery on the first MPJ;

(iii) intra-articular steroid, or any other intra-articular injection at the first MPJ in the previous 6 months;

(iv) treatment with systemic steroid (excluding inhalation or topical steroids), immunosuppressives or anticoagulants (except for acetylsalicylic acid at dosages of up to 325 mg/day);

(v) presence of joint infection(s) of the foot;

(vi) significant deformity of the first MPJ including hallux abducto valgus (grade of 3 or 4 scored using the Manchester Scale [20];

(vii) presence of peripheral vascular disease. Peripheral vascular disease will be considered to be present if any of the following are present [21];

▪ past history of, vascular surgery, Raynaud's phenomenon, vasculitis associated with connective tissue diseases, Buerger's disease, arterial emboli, deep vein thrombosis or lower limb ulcers;

▪ history of intermittent claudication or rest pain;

▪ presence of atrophy, ulcers or significant oedema;

▪ inability to palpate at least one pedal pulse;

▪ Ankle Brachial Pressure Index <0.9;

(viii) presence of one or more conditions that can confound pain and functional assessments of the first MPJ, such as metatarsalgia, plantar fasciitis, pre-dislocation syndrome, sprains of the foot, Achilles tendinopathy, degenerative joint disease of the foot (other than the first MPJ) or painful corns and callus;

(ix) planning to undergo any surgical procedure or receive any injections, apart from those dictated by the study, at the involved first MPJ during the study period;

(x) presence of systemic inflammatory condition or infection, such as inflammatory arthritis, diagnosed with rheumatoid arthritis, ankylosing spondylitis, psoriatic arthritis, reactive arthritis, septic arthritis, acute pseudogout, or any other connective tissue disease;

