### Intra-articular injections for the treatment groups

Participants will be randomised to receive a single intra-articular injection of up to 1 ml of hyaluronan (Synvisc^®^; Genzyme Biosurgery, Genzyme Corporation, NJ, USA) or sterile saline (placebo) into the first MPJ. Each 2 ml ampoule of Synvisc^® ^contains 16 mg of hylan G-F 20 (cross-linked hylan polymers; hylan A and B), 17 mg sodium chloride, 0.32 mg disodium hydrogen phosphate, 0.08 mg sodium dihydrogen phosphate monohydrate. The hyaluronan is extracted from chicken combs and the purified material has an average molecular weight of 6,000 kDa.

The injections will be performed by the same experienced interventional radiologist ([name]) using fluoroscopic imaging to ensure accurate deposition of the hyaluronan within the joint. As the Synvisc^® ^is provided in ampoules that are labelled with the product name, it will not be possible to blind the injector, however this person is not involved in generation of the allocation order, recruitment, assessment or data analysis. The intra-articular injection will be performed using a 21 gauge (0.80 × 19 mm) Surflo^® ^(Terumo^® ^Corp., Tokyo, Japan) winged infusion set under aseptic procedures. Either a dorso-lateral or dorso-medial approach for injection will be used at the discretion of the injector (depending on which approach provides minimum interference from the osteophytes at the first MPJ joint margins). No anaesthetic will be used. If the participant has bilateral painful first MPJs, only one side (the most painful side) will be treated and used for data collection. The injector will record the volume of the agent that is injected.

Participants will be given the option of a second and final intra-articular injection (of Synvisc^® ^or sterile saline according to the treatment group they are in) on days 30 or 90 if there is no improvement in pain (assessed using the VAPS for pain during walking or at rest) and the participant has not experienced severe adverse effects after the first injection).

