#### Primary outcome measures

Outcome measurements (primary and secondary) will occur at four time-points at baseline, 1, 3 and 6 months post-treatment (after the intra-articular injection of Synvisc^® ^or placebo). The assessor performing the measurements will be blinded as to which treatment group participants have been allocated to. Participants who receive a second treatment at day 30 or 90 will be followed for a further 30 days or 90 days respectively and undergo outcome measurements at 7 or 9 months respectively.

The primary outcome measures will be the *Pain *and *Function *subscales of the Foot Health Status Questionnaire (FHSQ) [24]. The FHSQ includes 13 questions that assess four domains of foot health, *Foot pain, Foot function, Footwear *and *General foot health*. The FHSQ has been subjected to an extensive validation (content, criterion and construct validity) process. It has a high test-retest reliability (intraclass correlation coefficients ranging from 0.74 to 0.92) and a high degree of internal consistency (Cronbach's α ranging from 0.85 to 0.88) [24]. Rigorous reviews have rated it as one of the highest quality foot health status measures currently available [25-27].

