### Statistical analysis

Statistical analysis will be undertaken using SPSS version 14.0 (SPSS Corp, Chicago, Ill, USA) and STATA 8 (Stata Corp, College Station, Tex., USA) statistical software. All analyses will be conducted on an intention-to-treat principle using all randomised participants [45-47]. Missing data will be replaced with the last score carried forward [48]. Standard tests for normal distribution will be used and transformation carried out if required.

Demographic characteristics (gender, age, weight, height, body mass index) will be determined for the baseline visit for each treatment group. Summary statistics will be calculated for duration of symptoms, side affected (left, right, bilateral), grade of OA at the first MPJ [19] as well as all primary and secondary outcome measurements for each treatment group.

Analyses will be conducted on 1, 3 and 6 month outcome measures. The continuously-scored outcome measures at 1, 3 and 6 months will be compared using analysis of covariance with baseline scores and intervention group entered as independent variables [49,50]. The exception to this will be the plantar pressure measurements which will be analysed at baseline, 1, 3 and 6 months using two-way repeated measures analysis of variance statistics. Post-hoc comparisons will be performed using Bonferroni-adjusted t-tests. Nominal and ordinal scaled data will be compared at 1, 3 and 6 months using Mann-Whitney U-tests and chi-square analyses (or Fisher's exact test where appropriate) respectively. Effect sizes will be determined using Cohen's *d *(continuous scaled data) or odds ratios (nominal scaled data and ordinal scaled data) as appropriate.

The outcome measurements obtained at 7 or 9 months for participants that receive a second and final intra-articular injection (of Synvisc^® ^or sterile saline according to the treatment group they are in) on days 30 or 90 respectively, will also be analysed as described above. These analyses will be classified as secondary outcomes.

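### The 7- and 9-month between-arm analysis is confined to re-injected participants, a subset formed after randomisation, and can be biased if Synvisc affects early pain, tolerability or uptake

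*Protocol article*

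**What the plan says.** All references are to the protocol article.

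- **Who is re-injected** (Intra-articular injections for the treatment groups). "Participants will be given the option of a second and final intra-articular injection". It is offered "if there is no improvement in pain (assessed using the VAPS for pain during walking or at rest") and provided "the participant has not experienced severe adverse effects after the first injection".
- **Who has later visits** (Primary outcome measures). "Participants who receive a second treatment at day 30 or 90 will be followed for a further 30 days or 90 days respectively", with measurements at 7 or 9 months. No such visits are described for anyone else.
- **How the later data are analysed** (Statistical analysis). "The outcome measurements obtained at 7 or 9 months for participants that receive a second and final intra-articular injection" at those days are to be handled like the main outcomes ("on days 30 or 90 respectively, will also be analysed as described above") and are classed as secondary. For continuous outcomes the main method is "analysis of covariance with baseline scores and intervention group entered as independent variables", with Cohen's d as the effect size.
- **General rule** (Statistical analysis). All analyses follow intention to treat in everyone randomised, with the last score carried forward for missing data.
- **Caveat** (Discussion). The authors accept that the second injection may make the results harder to interpret. They keep it because it resembles practice, and they give no analytic remedy.

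**The concern.** Randomisation makes the arms comparable at entry. The later analysis keeps only people who pass three steps that come after it: no improvement in pain, no severe adverse effects, and a decision to accept another injection. Treatment can influence each step. If Synvisc relieves early pain, fewer Synvisc participants qualify, and those who do have fallen further below their own arm's average than the saline participants who qualify. Adjusting for baseline score does not restore the balance, because the selection acts on what happened after baseline.

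At stake is a secondary result with p-values and effect sizes that readers would take as randomised evidence on later efficacy. The section also conflicts with itself, since an analysis limited to re-injected participants is not one of everyone randomised.

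**Working it through.** **Inputs from the Sample size section.** Difference 14 FHSQ pain points, SD 25, power 90%, significance level 0.05, 5% drop-out, 142 participants (71 per group), recruitment target about 75 per arm.

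**The plan's own figure.** A two-sided test of two means needs 68 per arm, and 68/0.95 rounds up to 72 per arm (144 in total), against the stated 142. Conversely, 71 × 0.95 = 67.45 per arm gives power 0.902. The stated size is reproduced to within two participants, so 14 and 25 are usable inputs here.

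**Assumptions not in the documents.** The SD of 25 applies to change. Mean early improvement is 20 points on Synvisc and 6 on saline, so the true effect is 14. Re-injection occurs whenever early change ≤ 0, with full uptake. Selection acts on the outcome scale itself. The second injection has no effect. The correlation r between early and late change is 0.4, 0.6 or 0.8.

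**Step 1: share re-injected,** P = Φ(−mean/25).
- Synvisc: Φ(−0.80) = 0.212, about 16 of 75.
- Saline: Φ(−0.24) = 0.405, about 30 of 75.

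**Step 2: distance of the selected people below their own arm's mean,** 25 × φ(mean/25)/P.
- Synvisc: 25 × 0.2897/0.2119 = 34.2 points.
- Saline: 25 × 0.3876/0.4052 = 23.9 points.
- Gap: 10.27 points. The selected groups' early changes average 20 − 34.2 = −14.2 and 6 − 23.9 = −17.9, so the arms already differ by 3.7 points rather than 14.

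**Step 3: late difference in the subset** = true late effect − r × 10.27.

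| r | True late effect 14 | True late effect 0 |
|---|---|---|
| 0.4 | 9.9 | −4.1 |
| 0.6 | 7.8 | −6.2 |
| 0.8 | 5.8 | −8.2 |

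The loss from a true 14 is 29% to 59%. With a smaller constant effect of 7 (20 versus 13), the subset shows 4.9, 3.8 and 2.8. If the two means are equal, the step 2 distances are equal and the bias is zero.

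**Step 4: the same question with the planned baseline-adjusted model.** A simulation of 400,000 participants per scenario used SD 25, an assumed saline improvement of 15 points, baseline-to-follow-up correlations of 0.3, 0.5 and 0.7, and a month-1-to-late correlation 0.2 higher.

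| True effect (month 1, late) | All randomised | Non-improvers only (0.3, 0.5, 0.7) |
|---|---|---|
| 14, 14 | 13.9 to 14.0 | 9.6, 8.0, 5.0 |
| 14, 0 | about 0 | −4.2, −6.1, −8.7 |
| 0, 0 | about 0 | about 0 |

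Baseline adjustment therefore does not remove the bias.

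**Step 5: precision.** With 16 versus 30 people the standard error is 25 × √(1/16 + 1/30) = 7.74. Power for 14 points is Φ(14/7.74 − 1.96) = 0.44 before any bias, and lower once the subset is split between months 7 and 9.

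**The case against.** The strongest defence is that these analyses are classed as secondary, that the Discussion admits the second injection complicates interpretation, and that the randomised comparisons at 1, 3 and 6 months do not depend on them. That stands, and it limits the severity. It does not cure the analysis: the secondary label still leaves between-arm tests and effect sizes, and the caveat comes with no remedy. Nor is this detail that a fuller plan might supply, because the article itself fixes the method.

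The sizes above are also open to challenge. The improvements and correlations are assumed, and the SD of 25 is not described as an SD of change. Selection is modelled on the outcome itself, whereas the protocol selects on a visual analogue scale of walking or rest pain; a weaker link between that scale and the FHSQ would shrink the bias. Uptake may be partial, and there are two decision days rather than one. All of this stands, so the figures are illustrations and not forecasts.

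Two further defects might be inferred, but the text does not support them.
- *That earlier scores will be carried forward into 7- and 9-month visits most participants never had.* The sentence limits the analysis to measurements obtained in re-injected participants, and visits never scheduled are not naturally missing data. What remains is a conflict with the general all-randomised rule.
- *That the later visits escape the paracetamol washout.* The washout applies before "follow-up assessments at 1, 3 and 6 months after the treatment", and inclusion criterion (ix) runs the study period to six months after the final treatment. Months 7 and 9 are six months after injections at days 30 and 90, so the washout can be read as covering them. Any gap would apply equally to both arms.

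**Conclusion.** The point holds. The plan specifies a between-arm efficacy analysis at 7 and 9 months in a subset formed by response, tolerability and choice after randomisation, and this contradicts its own statement that all analyses include everyone randomised.

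A reader might go further and conclude that the analysis is bound to mis-state the effect. The documents do not support that. Bias requires Synvisc to affect early pain, tolerability or uptake; if it affects none of them, there is none. Under the assumptions shown, with selection on pain alone, the bias runs against Synvisc: a true 14 points appears as about 10 to 6, and a late effect of zero appears as 4 to 8 points of harm. Selection through tolerability or uptake could differ in size and direction.

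Nor does this defect undermine the trial's main comparisons at 1, 3 and 6 months. It should be fixed, but it is not critical to the trial's primary conclusions.

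**What to change.** Replace the sentence on the 7- and 9-month outcomes in the Statistical analysis section so that it:

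1. reports these data descriptively by arm, as means and within-person change;
2. labels them as a non-randomised subset defined by response, tolerability and choice after the first injection;
3. gives no between-arm p-values or effect sizes;
4. exempts them from the all-randomised and last-score-carried-forward statements;
5. rests efficacy conclusions on the 1, 3 and 6 month comparisons of everyone randomised.

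The cost is a change of wording, with no change to visits or treatment. The downside is the loss of an apparent secondary efficacy comparison, which the design could not support as a randomised one.

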## Discussion

This study is a randomised placebo controlled trial designed to investigate the efficacy of intra-articular hyaluronan (Synvisc^®^) to reduce pain and improve function in people with OA of the first MPJ (hallux limitus). Two studies have previously investigated the efficacy of intra-articular hyaluronan for the treatment of first MPJ OA [13,14]. However, neither of these studies used a placebo control group. To our knowledge, this is the first randomised controlled trial using intra-articular hyaluronan for OA of the first MPJ.

The use of a placebo control group is essential for studies evaluating the effects of intra-articular therapies as there is likely to be a large placebo response related to the injection procedure and this may inflate the results in uncontrolled evaluations [51]. Indeed, a recent meta-analysis of hyaluronan for knee OA concluded that a placebo effect accounted for 79% of the efficacy of intra-articular hyaluronan [16].

The study protocol and outcome measures have been developed in accordance of the recommendations of the OARSI Clinical Trials Task Force guidelines [18]. The outcome measures are pain and function subscales of the FHSQ, pain and stiffness at the first MPJ, range of motion (dorsiflexion) of the first MPJ, plantar flexion strength of muscles of the first MPJ, generic health related quality of life (SF-36), patient satisfaction with treatment, consumption of rescue medication as well as frequency and nature of adverse effects. These outcomes will be measured at baseline then at 1, 3 and 6 months after treatment. Previous research suggests that the effects of intra-articular hyaluronan persist for up to 12 months following treatment [9,38]. Thus, the use of follow-up assessments at 6 month post-treatment will allow us to determine if the effects, if any, of intra-articular hyaluronan persist in the longer term.

Participants will be given the option of a second and final intra-articular injection (of Synvisc^® ^or sterile saline according to the treatment group they are in) on days 30 or 90 if there is no improvement in their symptoms. Although this has the potential to complicate the interpretation of the results of the study, this protocol was included as it is likely to be more reflective of clinical practice [14], and this is in keeping with the pragmatic nature of this trial.

In summary, this project is the first randomised controlled trial to be conducted to evaluate the efficacy of intra-articular hyaluronan for reducing pain and improving function in people with hallux limitus. The study protocol, including interventions, have been pragmatically designed to ensure that the study findings are generaliseable to clinical practice. Recruitment for the study will commence in June 2008, and we expect final results to be available in mid-2010.
